### Sample size

With no data on TRF interventions in subjects within our age range, an exact calculation of sample size is not feasible. To estimate sample size, we relayed on our data from more than 150 patients with obesity (8–18 years of age) at the Hospital’s Endocrinology department that have undergone the standard obesity treatment protocol. This group would be equivalent to the Control group. The standard deviation of BMI-SDS change over a period of 2 months during a lifestyle intervention was 0.35 units. Based on these data, with type I error of 0.05 and power set at 80%, we will need 64 subjects to detect a difference of 0.25 units in BMI-SDS change between groups. To account for a potential high drop-out rate, we aim to recruit a total of 80 subjects, anticipating up to a 20% participant loss.

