### Randomization

Participants are randomly allocated into Control and TRF groups with an allocation ratio of 1:1. Randomization is performed in blocks (block size of 4) stratifying by gender and age (younger/older than 12 years of age) to allow for a balanced number of participants in each group. Randomization lists were obtained from computer-generated sequences. Participant randomization is implemented in REDCap (Research Electronic Data Capture).

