### Data management and analysis

Study data are collected, managed, and stored using REDCap tools hosted at Hospital Sant Joan de Déu (15, 16). REDCap is a secure, web-based software platform designed to support data capture for research studies. To assess the comparability of the two groups, continuous variables will be compared using Student’s *t*-test or non-parametric tests for those with a non-normal distribution. Categorical variables will be assessed with the Chi-square test. Multivariate linear and logistic regression models will be used to analyze the effects of the TRF intervention in comparison with the Control group. These methods will allow for adjustment by potential confounding variables, including gender, age, baseline BMI-SDS, and pubertal status. Furthermore, the design of the study allows for secondary analyses. Specifically, we will carefully examine whether (1) gender; and (2) pubertal status are determinants of the short- and long-term TRF-induced effects by analyzing the different data subsets. Statistical calculations will be performed in JMP v16 software (SAS Institute Inc., Cary, NC).

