Genetic evidence in animal models supports a causal role of circadian rhythm disruptions in inducing metabolic derangements, including hyperglycemia, hyperinsulinemia, impaired lipid metabolism, and hepatic steatosis (24–28). In agreement, alterations in circadian systems may contribute to obesity-related complications in humans, including T2D and hypertension (29–36). In recent years, several studies have unveiled a functional interaction between circadian rhythms and the gut microbiome that may influence host metabolism and glucose homeostasis (37–40). The gut microbiome itself has been shown to be an important player in the development of obesity and T2D (41–43). Despite all these data, further evidence is needed to determine whether this gut microbiota-circadian clock axis plays a role in the development of obesity and metabolic diseases.

Limitations of this study include a potential high drop-out rate in young children; while studies in adults and adolescents generally show high adherence to the intervention, no data are available for young children. In these regards, we have anticipated a 20% drop-out rate when calculating sample size. Second, all participants will be from the same geographical area (mostly Barcelona’s metropolitan area); therefore, caution will need to be exerted when extrapolating the results to other populations. Third, while the study will be powered for the analysis of the main outcome, secondary analysis with data subsets (namely, gender and pubertal status) may be underpowered. Finally, because of ethical reasons we cannot include a group of children and adolescent with obesity with no intervention as all patients receive treatment at the hospital.

In summary, this study will assess the safety and efficacy of a TRF intervention in children and adolescents with obesity and determine the long-term effects of the intervention. Positive results from this study will provide new evidence-based tools to endocrinologists, dieticians, and other practitioners to tackle childhood obesity.

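### Separate subset analyses cannot show whether gender or pubertal status changes the TRF effect; an interaction term in the full sample can

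*Protocol article*

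**What the plan says.** Under Data management and analysis, the article plans linear and logistic regression for TRF against Control, with gender, age, baseline BMI-SDS and pubertal status as adjustment variables. It then announces secondary analyses to examine whether gender and "pubertal status are determinants of the short- and long-term TRF-induced effects by analyzing the different data subsets". Neither this section nor any other names a treatment-by-gender or treatment-by-pubertal-status term, or any other comparison between subsets.

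The limitations in the Discussion return to the same analyses and say that "secondary analysis with data subsets (namely, gender and pubertal status) may be underpowered". They give no other caution about interpretation.

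**The concern.** To call a factor a determinant of a treatment effect is to say that the effect differs between levels of that factor. The quantity needed is the difference between two treatment effects, with its own standard error. Analysing girls and boys separately yields two effects and two p-values, but not that difference. Adjusting for gender and pubertal status does not supply it either: as main effects they shift the outcome level and leave a single common treatment effect.

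The caveat about power does not repair this. Low power is usually taken as a warning that real effects may be missed. When two small subsets are set side by side, it has a second consequence: one can reach significance and the other miss it by chance alone. A reader can then come away believing that TRF works in girls but not boys, or after puberty but not before, when the effects are the same. These are the only two effect modifiers the article names, so such a statement could influence which children are offered TRF.

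**Working it through.** **Inputs**

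- Sample size section: "The standard deviation of BMI-SDS change over a period of 2 months during a lifestyle intervention was 0.35 units"; "we will need 64 subjects to detect a difference of 0.25 units in BMI-SDS change between groups"; type I error 0.05 and power 80%. Sidedness is not stated; two-sided is assumed.
- Sample size section: "we aim to recruit a total of 80 subjects, anticipating up to a 20% participant loss".
- Randomization section: participants are "randomly allocated into Control and TRF groups with an allocation ratio of 1:1", with stratification by gender and by age at 12 years, but not by pubertal status.
- Recruitment and eligibility criteria: about half of the participants are expected to be female.
- Pubertal split: not given. Equal halves are assumed first, then varied.

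**The plan's own figure.** By the normal approximation, n per arm = 2 × (1.960 + 0.842)² × 0.35² / 0.25² = 30.8, so 31 per arm and 62 in total. By the two-sample t-test, n = 31.76, so 32 per arm and 64 in total, which matches. Allowing for 20% loss, 64 / 0.80 = 80, which also matches.

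**Power within one subset.** With 64 evaluable, two equal subsets and 1:1 allocation, there are 16 per arm per subset.

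- SE of the subset effect = 0.35 × √(2/16) = 0.124.
- Noncentrality = 0.25 / 0.124 = 2.02, against a critical t of 2.042 on 30 df.
- Power = 49.8%.

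**Chance that exactly one subset is significant when the effect is the same in both.** The subsets are independent, so this is pA(1 − pB) + pB(1 − pA).

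- 64 evaluable: 2 × 0.498 × 0.502 = 0.500. A simulation of 40,000 trials gave 0.501.
- 80 evaluable (20 per arm per subset, power 59.5%): 2 × 0.595 × 0.405 = 0.482.

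**Dependence on the common true effect** (64 evaluable, equal halves):

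| Common effect (BMI-SDS) | Power per subset | Exactly one significant |
|---|---|---|
| 0 | 0.050 | 0.095 |
| 0.10 | 0.123 | 0.215 |
| 0.15 | 0.217 | 0.339 |
| 0.20 | 0.346 | 0.453 |
| 0.25 | 0.498 | 0.500 |
| 0.30 | 0.650 | 0.455 |
| 0.40 | 0.878 | 0.213 |

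For equal halves the expression is 2p(1 − p), which cannot exceed 0.50. The design effect happens to sit at that ceiling.

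**Dependence on the split** (64 evaluable, common effect 0.25):

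| Split | Power, smaller / larger subset | Exactly one significant |
|---|---|---|
| 40/60 | 0.410 / 0.577 | 0.514 |
| 30/70 | 0.315 / 0.647 | 0.554 |
| 20/80 | 0.214 / 0.707 | 0.619 |

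**The interaction test.** With four cells of 16, the SE of the difference between subset effects is 0.35 × √(4/16) = 0.175. That is twice the main-effect SE of 0.35 × √(2/32) = 0.0875.

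- Simulated false-positive rate when the effects are equal: 5.0%.
- Difference detectable with 80% power: 0.175 × 2.802 = 0.49. With 80 evaluable: 0.35 × √(4/20) × 2.802 = 0.44.
- Power for a difference of 0.25 between subset effects: about 30%.

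These figures are unadjusted and apply at 2 months. The article gives no SD of change at 12 or 24 months, so nothing comparable can be computed for the long-term effects.

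**The case against.** The strongest reply is that the article never states the faulty rule. It does not say that significance in one subset and not the other will count as a difference. Analysing subsets is compatible with setting estimates and intervals side by side, or with an interaction test described in a fuller document. This stands in part. A reader might infer that the plan commits itself to comparing p-values; the text does not support that, and the 50% is conditional on such a reading. What remains is that the article poses the question and names the means of answering it, and the means named supplies no contrast between subsets. This is therefore a stated method, not merely a detail left to the analysis plan.

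A second reply is that 50% is a worst case. It is, for equal halves, and it should not be quoted without its conditions. The article says there are no TRF data in this age range, and it cites an adolescent TRF trial that found no effect, so 0.25 is not a safe expectation. Away from 0.25 the figure falls, to 9.5% at no effect. It still exceeds 5% at every effect tabulated. The two rates are also different in kind: the 50% is a chance of discordant p-values and becomes an error rate only if discordance is read as a difference, whereas the 5% is the error rate of a test.

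A third reply is that these are secondary analyses with an acknowledged power limitation. That is correct and sets the weight of the point.

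**Conclusion.** The point holds as a weakness of method in a secondary analysis. The stated approach cannot answer the stated question, and the caveat about power does not address this. If subset significance were compared, a common 2-month effect of 0.25 would give discordant results about half the time (50% with 64 evaluable, 48% with 80, equal halves). At that effect, with 64 evaluable, pubertal splits from 40/60 to 20/80 give 51% to 62%. An interaction test would err 5% of the time. The figures assume two-sided tests at 0.05, SD 0.35 in every cell, arms balanced within subsets and no covariate adjustment; adjustment that reduced the residual SD would change them.

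Two stronger conclusions are tempting and unsupported. One is that the trial will report false subgroup differences half the time: this needs both a decision rule the article does not state and an effect near 0.25. The other is that the trial's main result is at risk: the primary comparison, sample size and randomisation are untouched. For the long-term effects the logic is the same, but no size can be attached.

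**What to change.** Replace the reference to analysing data subsets with wording such as:

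> *Whether the TRF effect differs by gender or by baseline pubertal status will be assessed by adding the treatment-by-factor interaction, one factor at a time, to the adjusted model fitted to all participants. Each interaction estimate will be reported with its 95% confidence interval. Subset estimates with confidence intervals will be descriptive, and no subgroup difference will be claimed without support from the interaction.*

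Naming baseline pubertal status matters because puberty will advance during 24 months of follow-up, and the modifier should be fixed before treatment.

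Optionally, extend the limitation in the Discussion to say that, unadjusted, only differences of about 0.44 to 0.49 BMI-SDS between subgroup effects at 2 months are detectable with 80% power. A non-significant interaction would then not be read as showing equal effects.

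The cost is a change of wording. It needs no further participants, data or software.

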## Discussion

Given the current status of the obesity epidemic and the fact that most children with obesity will track adiposity into adulthood, developing novel and more efficient strategies to tackle childhood obesity is an urgent need. TRF interventions are emerging as a promising strategy to treat obesity and improve metabolic status in adult subjects (8). However, very limited data are available describing this type of interventions in children and adolescents. A study with forty-five adolescents (age range 12–17) with intermittent energy restriction showed metabolic improvements (17). The intervention consisted in a very low-calorie diet for 3 days per week and achieved reductions in BMI and body fat as well as in several cardiovascular risk markers. Furthermore, a recent report showed no effects of a TRF intervention in a study with fifty adolescents (age range 14–18) (18). This intervention implemented a feed time restriction of 8 h, similar to our study; however, it differed in the length of the intervention (3 months) and the number of days per week with time restrictions (5 days per week). To our knowledge, the TRansForm study is the first to test a TRF intervention in children with obesity as young as 8 years of age. This study will evaluate the safety and efficacy of this intervention in this pediatric population with obesity.

The clinical study will also provide valuable information on circadian rhythm patterns in children and adolescences with obesity. Circadian rhythms are physiological processes that primarily respond to light and dark cycles [for review see (19)]. These are controlled by an internal circadian clock and are crucial in multiple important functions in mammals, including sleep patterns, eating habits, hormone release, and body temperature (19, 20). Notably, TRF interventions seem to exert their beneficial effects, at least in part, through modulating the circadian rhythm (21). Indeed, peripheral tissues, including liver or white adipose tissue, set their endogenous rhythmicity in response not only to light-dark cycle cues (through hypothalamic signals) but also to nutritional cues (22, 23). Hence, restrictions in feeding times modulate the rhythmic behavior of peripheral tissues, thereby impacting metabolic outcomes.

Genetic evidence in animal models supports a causal role of circadian rhythm disruptions in inducing metabolic derangements, including hyperglycemia, hyperinsulinemia, impaired lipid metabolism, and hepatic steatosis (24–28). In agreement, alterations in circadian systems may contribute to obesity-related complications in humans, including T2D and hypertension (29–36). In recent years, several studies have unveiled a functional interaction between circadian rhythms and the gut microbiome that may influence host metabolism and glucose homeostasis (37–40). The gut microbiome itself has been shown to be an important player in the development of obesity and T2D (41–43). Despite all these data, further evidence is needed to determine whether this gut microbiota-circadian clock axis plays a role in the development of obesity and metabolic diseases.

Limitations of this study include a potential high drop-out rate in young children; while studies in adults and adolescents generally show high adherence to the intervention, no data are available for young children. In these regards, we have anticipated a 20% drop-out rate when calculating sample size. Second, all participants will be from the same geographical area (mostly Barcelona’s metropolitan area); therefore, caution will need to be exerted when extrapolating the results to other populations. Third, while the study will be powered for the analysis of the main outcome, secondary analysis with data subsets (namely, gender and pubertal status) may be underpowered. Finally, because of ethical reasons we cannot include a group of children and adolescent with obesity with no intervention as all patients receive treatment at the hospital.

In summary, this study will assess the safety and efficacy of a TRF intervention in children and adolescents with obesity and determine the long-term effects of the intervention. Positive results from this study will provide new evidence-based tools to endocrinologists, dieticians, and other practitioners to tackle childhood obesity.

## Ethics statement

The studies involving human participants were reviewed and approved by Comitè d’Ètica d’Investigació amb medicaments (CEIm), Hospital Sant Joan de Déu, University of Barcelona (Spain). Written informed consent to participate in this study was provided by the participants’ legal guardian/next of kin.
